## Abstract

**Background:**

Up to 15% of pregnant women suffer from antenatal depression, and there is mounting evidence that the consequences can be devastating for both the woman and her child. Identifying effective treatments is crucial to avoiding the harmful consequences of unrecognized and untreated depression.

**Methods:**

This ongoing research project evaluates the efficacy of the *Stronger Together* internet-assisted cognitive behavioral therapy (iCBT) with telephone coaching for antenatal depression. It is a large, population-based, two-parallel group, randomized controlled trial. The overarching hypothesis is that iCBT programs are easy to access and affordable and will reduce self-reported symptoms of antenatal depression better than an educational control. The intervention group is also expected to report fewer anxiety symptoms after treatment than the control group. The protocol follows the Standard Protocol Items: Recommendations for Interventional Trials (SPIRIT) guidelines. The study population consists of all Finnish- or Swedish-speaking women, aged ≥18 years, who attend maternity health check-ups at 13–18 weeks of gestation in selected areas of Finland. The aim is to recruit all women who exceed 10 points on the Edinburgh Postnatal Depression Scale and meet other eligibility criteria. Other measures used are the Beck Depression Inventory-II, the Generalized Anxiety Disorder 7-Item Scale, the Pregnancy-Related Anxiety Questionnaire-Revised, the Social Phobia Inventory, and the Perceived Stress Scale. In addition, biological samples (maternal sera and buccal cells) are collected to explore possible moderators for the treatment response. The primary data are collected at baseline and 11 weeks after randomization. The women are randomized 1:1 to the *Stronger Together* iCBT intervention, which combines seven-weekly themes on a digital platform with weekly telephone coaching, or the educational control group. The CBT components include psychoeducation, behavioral activation, coping with social relationships, cognitive restructuring, and preventing setbacks. The educational control group receives psychoeducational material about wellbeing during pregnancy. Both groups continue to receive standard treatment and maternity health check-ups.

**Discussion:**

We hypothesize that the *Stronger Together* iCBT intervention will reduce self-rated symptoms of antenatal depression, general and pregnancy-related anxiety, social phobia, and stress. The intervention may offer an accessible and effective treatment for depressed pregnant women.

**Clinical Trial Registration:**

ClinicalTrials.gov, identifier ID NCT04223115, Date of first registration: January 10, 2020.

## Introduction

1

Antenatal depression is a significant public health problem: as many as 10%–15% of pregnant women report depressive symptoms (1–3). Antenatal depression has been associated with preterm birth and low birth weight (4, 5), postnatal depression (6), and attachment difficulties between mother and infant (7). Previous studies on the long-term impact of maternal perinatal depression have also reported increased risks for behavioral problems, learning difficulties, and depression in offspring (8). It is crucial to provide empirically supported interventions at early time points, as most depressive symptoms emerge during pregnancy rather than after delivery (9). Early psychosocial interventions are also important because of concerns that selective serotonin reuptake inhibitors during pregnancy may be harmful to offspring development (10, 11).

Evidence-based psychosocial treatments, such as cognitive behavioral therapy (CBT) and interpersonal psychotherapy, are the first-line treatment options for antenatal depression (12, 13). A meta-analysis of 6,270 participants from 43 trials examined the efficacy of psychosocial treatments for depression during pregnancy. The overall effect size was moderate (g = 0.67, 95% confidence interval 0.45–0.89) (14). This finding was in line with the efficacy of psychosocial treatments for adult depression in general (15). Studies have not observed differences between the main types of psychosocial treatments and how they are delivered for depression (15, 16). Consequently, psychotherapies are also feasible for pregnant women, regardless of whether they are delivered face-to-face, individually, or in groups (13, 17). Digitally delivered internet-assisted CBT (iCBT) reduces logistical and practical barriers, including childcare, transport, and scheduling difficulties; meta-analyses have found significant treatment effects for general and perinatal depression (14, 15, 18). However, most previous studies have focused on the postpartum period, and the evidence for antenatal interventions is limited (19–22).

Previous randomized controlled trials (RCTs) on iCBT for antenatal depression have reported promising efficacy for reducing core symptoms of depression (21, 23, 24) with high acceptability of the iCBT interventions (21, 23). Attrition rates have been lower in guided than unguided iCBTs (18, 19, 23), and guided programs had higher effect sizes (19). However, studies on iCBT for antenatal depression have relied on small sample sizes and measured outcomes with self-reports only, posing a risk for overall assessment bias (19). No previous evidence exists of the effectiveness of iCBT for symptoms of antenatal depression in pregnant women screened at the population level. Larger population-based studies are needed to replicate previous findings from smaller studies and to identify effective treatment options for pregnant women whose mental health problems impact not only themselves but their offspring as well.

The aim of this study is to examine the efficacy of the *Stronger Together* iCBT intervention for symptoms of antenatal depression in adult pregnant women in Finland. An ideal antenatal iCBT intervention should facilitate and integrate service systems so that symptoms of antenatal depression are identified early and women have easy access to empirically supported treatments. The objectives of this study are to evaluate symptoms of antenatal depression among adult pregnant women in Finland using population-based screening, evaluate the efficacy of the Stronger Together iCBT intervention for treating symptoms of antenatal depression, and examine possible treatment moderators. The primary hypothesis is that the iCBT intervention will reduce self-reported symptoms of antenatal depression, measured by the Edinburgh Postnatal Depression Scale (EPDS), compared to the educational information (allocation ratio 1:1). The secondary hypothesis is that the iCBT intervention group will report fewer symptoms of generalized anxiety, pregnancy-related anxiety, and personal stress after treatment than the educational control group. This hypothesis is based on the literature; psychosocial interventions for perinatal depression have been found to be effective also for anxiety and stress (12).

## Methods

2

### Study type and design

2.1

This study is a two-parallel group RCT. The study subjects and intervention coaches are open to the treatment code, but the statistician and researchers stay blinded until a blind review is conducted for the primary and secondary outcome variables. Blinding is an established approach in clinical trials to minimize the risk of performance and detection bias. Clinical trial guidelines recommend that statisticians remain blinded to allocation prior to the final analysis (25). In this RCT, pregnant women with depressive symptoms are randomized 1:1, by study site, into the *Stronger Together* iCBT intervention with telephone coaching or the educational control group. Both groups also receive standard treatment, according to established regional standard care guidelines, and this may involve therapy and medication. However, ongoing psychotherapy at recruitment is an exclusion criterion (**Table 1**). The study outline is presented in **Figure 1**.

**Table 1 T1:** Inclusion and exclusion criteria.

Inclusion	Exclusion
- Age ≥ 18 years - Fluent in written and spoken Finnish or Swedish - Access to computer or mobile phone with internet/internet literacy - 12–22 weeks pregnant - EPDS score of ≥10 at screening and ≥9 at baseline	- Lifetime history of psychotic disorders, including schizophrenia, schizoaffective disorder, bipolar disorder, and psychotic depression - Active suicidal ideation - Severe substance abuse or dependence - Active ongoing psychotherapy - Already participating in another intervention study to treat the symptoms of antenatal depression - Expecting multiple births

EPDS, Edinburgh Postnatal Depression Scale.

**Figure 1 f1:**
[figure not shown]
Flowchart of the RCT study. RCT, randomized controlled trial.

### Recruitment

2.2

Finnish maternity clinics provide regular check-ups 11–15 times during pregnancy to monitor the wellbeing of the fetus, the pregnant woman, and the whole family. Up to 99.8% of pregnant women in Finland use these services each year (26). This RCT consists of all the women attending regular maternity check-ups in the Wellbeing Services Counties of Southwest Finland, Central Ostrobothnia, and Siun Sote, and the cities of Espoo, Tampere, Pori, and Oulu. These areas account for approximately 14,000 live births per year, which is nearly one-third of the infants born in Finland each year (27). The women are screened using the EPDS, which is one of the most widely studied and validated self-report instruments for depressive symptoms during the perinatal period (28). Finnish national care guidelines state that the EPDS should be routinely used during health check-ups at 13–18 weeks of gestation.

All the women attending maternity clinics in the study areas are given an envelope during the first face-to-face health visit at 8–10 weeks of gestation. This includes an information letter, an informed consent document, and the EPDS questionnaire. Healthcare professionals also give the women verbal information about the ongoing study. The women are asked to complete the forms by the next clinic check-up at 13–18 weeks and provide informed consent if the research team is allowed to contact them about taking part in the RCT. The women are also provided with contact details for the study team in case they have any questions.

The informed consent forms and the EPDS questionnaires are collected during the routine check-up at 13–18 weeks. The women can fill in the forms during their visit if they have forgotten them. Scores of 10 points or more on the EPDS scale of 0 to 30 indicate possible depression. Those who have reached these scores and agreed to be contacted by the study group are invited to undergo an eligibility assessment for the RCT. As the EPDS form is routinely used by maternity health clinics, any symptoms are also discussed with the public health nurses working in the clinics. The public health nurses can contact the research group if they have any questions. The study coaches contact the public health nurses, regularly supporting them with the recruitment and other possible matters. Recruitment in the study is still ongoing in all participating areas.

### Eligibility criteria

2.3

The study coaches call the women to introduce the study in more detail and screen them for eligibility, according to the inclusion and exclusion criteria in **Table 1**. The coaches are specially trained to deliver the intervention, and they receive weekly supervision from two senior CBT therapists. Phone calls are recorded for quality control.

If the woman is eligible, she is asked to provide informed consent on a secure website. At the start of the baseline assessments, the women fill in the EPDS again to assess how stable their depressive symptoms are. If they score at least 9 points, they proceed to the full digital baseline assessment. If they score 8 points or less, they are excluded. A separate phone call is made after the baseline questionnaires. In this phone interview, the women are assessed using selected sections of the structured diagnostic interview, Mini-International Neuropsychiatric Interview (MINI) (29). The included sections cover depression, suicidality, bipolar disorder, and anxiety disorders. If the woman reports current suicidality, she is excluded from the study and referred to appropriate services. Other exclusion criteria include psychotic and bipolar disorders, substance abuse, active ongoing psychotherapy, participating in another intervention, and multiple pregnancy (**Table 1**). The women can be referred to local healthcare services if more individual treatment is considered necessary, and the coaches can also consult a psychiatry specialist at any time.

### Intervention

2.4

*Stronger Together* is a targeted iCBT intervention for pregnant women with depressive symptoms who score ≥9 points on the EPDS. It is based on the *Coping with Depression* course, which has been effective in preventing and treating depression in several RCTs and has been implemented in different target populations and settings (30). The highly structured *Stronger Together* intervention includes basic CBT components: psychoeducation, behavioral activation, coping with social relationships, cognitive restructuring, and preventing setbacks (**Table 2**). It comprises seven-weekly themes on a digital platform and weekly phone coaching. There will also be two booster sessions, approximately 2 and 7 months after the birth, including a phone call and a digital component. No physical visits or face-to-face communication are included. The aim is to strengthen the expectant mother’s coping skills. The phone coaches are specially trained healthcare professionals who support and motivate the women. The weekly phone sessions are scheduled when they are most convenient for the women. To ensure the fidelity and quality of the intervention, the phone coaches receive weekly supervision by two experienced CBT therapists, including case consultations, intervention management, and support on the use of CBT principles during the coaching process.

**Table 2 T2:** Core components of the stronger together iCBT intervention.

Theme	Key elements	Skills and tools
Introducing the intervention	Psychoeducation, CBT model, working alliance	Monitoring mood/mood diary and mood compass
1. Body sensations and mood	Healthy life habits, changes in body during pregnancy, body sensations	Relaxation, regular exercise/mood diary, mood compass
2. Behavior and mood	Behavioral activation	Listing pleasant activities/mood diary, mood compass
3. Improving mood through pleasant activities	Increasing behavioral activation	Planning ahead/mood diary, mood compass, activity schedule
4. Keeping up social relationships	Social networks	Asking for help/mood diary
5. Mood and thinking	Positive and negative thinking, negative cognitive bias	Recognizing positive and negative thoughts/mood diary, mood compass
6. Realistic thinking and self-compassion	Cognitive restructuring	Choosing positive thoughts/mood diary, mood compass
7. Preventing setbacks	Useful skills, monitoring mood diary, skills summary, future plans	Self-checking/mood diary, future plans

iCBT, internet-assisted cognitive behavioral therapy.

### Educational control group

2.5

The control group receives access to digitally delivered psychoeducational material, which includes information about pregnancy-related life changes, social relationships, wellbeing, and healthy habits such as regular exercise, sleep, and coping with stress. The controls do not receive weekly phone coaching or access to the core CBT components. The controls receive standard prenatal care at the maternity clinics.

### Adverse events

2.6

*Stronger Together* is a minimal-risk trial based on CBT, which is considered the first-line treatment for depression. CBT has no significant adverse effects, and we do not anticipate that the intervention will have negative side effects. Any adverse effects that do occur are handled during the weekly phone calls, and the women can also contact the study team at any time.

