### Primary outcome

2.7

The primary outcome variable is any change in the total EPDS score (31) from baseline at 13–18 weeks of gestation to 11 weeks after randomization. The EPDS is a standard 10-item self-report questionnaire, which was originally developed to screen for postpartum depression. It has been widely validated to detect depression both during (Cronbach’s α = 0.82–0.84) (32) and after pregnancy (Cronbach’s α = 0.87) (31). However, it has not been validated specifically in Finland. The respondents are asked about symptoms of depression in the past week. The score ranges from 0 to 30, and 13 points or above is normally used as a cutoff for depression during pregnancy. Because this study focuses on early intervention, we use a cutoff of 10 points on the total EPDS score to ensure that we include pregnant women with subclinical depressive symptoms (18, 33). The primary and secondary outcomes have been described in detail in **Table 3**.

**Table 3 T3:** The schedule of enrollment, interventions, and assessments.

	Enrollment		Allocation	Post-allocation		
Time point		T0		Intervention period	T1	T2
Enrollment						
EPDS screen	X					
Informed consent	X					
Eligibility screen	X					
MINI interview	X					
Allocation			X			
Intervention						
iCBT intervention group				iCBT with telephone coaching		
Educational control group				Online psychoeducation		
Assessments						
*Depression*						
Symptoms of antenatal depression (primary outcome) EPDS		X				X
Depressive symptoms BDI-II		X				X
*Anxiety*						
Generalized anxiety GAD-7		X				X
Pregnancy-related anxiety PRAQ-R2		X				X
Social phobia SPIN		X				X
*Other measures*						
Maternal attachment MAAS		X				X
Perceived stress PSS		X				
Quality of life and sleep		X				X
*Treatment-related measures*						
Alliance WAI-SR					X	
Use of the digital content					X	
Satisfaction CSQ-I					X	
Biological samples						
Serum sample		X				
Buccal cell swab		X				X

T0 is baseline, T1 is immediately after the intervention, and T2 is 11 weeks after randomization.

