### Power

2.15

The aim of the power calculations was to determine how many subjects should be enrolled in the intervention and control groups to achieve 80% power to reject the null hypothesis of equal means. The power calculations were based on a population mean difference of μ1 − μ2 = 9.0 − 10.5 = −1.5 in EPDS scores, with a standard deviation of 6.30 for both groups and a significance level of α = 0.05. This resulted in 278 subjects in both groups. Because we anticipate 14% attrition in both groups, we aim to enroll 317 dyads in both groups. To promote participant retention, each subject will receive reminders by email and telephone from the study coaches. No further data will be collected if a participant chooses to withdraw from the study. If a participant discontinues the intervention but does not withdraw from the study, data will be collected according to the protocol.

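### The only scheduled contact named for adverse effects exists in the iCBT arm alone, so adverse-event counts gathered that way would not be comparable between arms

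*Protocol article*

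**What the plan says.** Section 2.6 (Adverse events) covers the trial as a whole. It gives the expectation that "we do not anticipate that the intervention will have negative side effects" and then names two routes for any that arise. The first is scheduled: "Any adverse effects that do occur are handled during the weekly phone calls". The second is open-ended: "the women can also contact the study team at any time".

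Section 2.4 places the weekly calls inside the intervention: "It comprises seven-weekly themes on a digital platform and weekly phone coaching". Section 2.5 says of the other arm: "The controls do not receive weekly phone coaching or access to the core CBT components". It adds: "The controls receive standard prenatal care at the maternity clinics".

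Table 3 ("The schedule of enrollment, interventions, and assessments") lists EPDS, BDI-II and GAD-7 at T0 and T2 with no restriction by arm. At T1 it lists only the treatment-related measures, which section 2.12 restricts to the intervention group. Section 2.15 says that "each subject will receive reminders by email and telephone from the study coaches", with retention as the stated purpose. Section 2.16 describes no between-arm analysis of adverse events.

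**The concern.** In a two-arm trial, recorded adverse events can be compared only if both arms have a similar opportunity to report them. Here one arm speaks to a coach every week and the other does not, and both subjects and coaches know the allocation (section 2.1). With equal true rates, the arm in more frequent contact would be expected to have more events on record.

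Two things are at stake. A table of adverse events by arm could show an excess under iCBT that reflects contact frequency and not the treatment. And the stated expectation of no negative side effects could not be checked fairly from those counts, since there would be no like-for-like comparison arm.

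**Working it through.** The article gives no adverse-event rate, harms endpoint or harms test, so there is no stated figure to reproduce. The check is a comparison of sections, followed by an illustration.

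**Routes for adverse effects, by arm**

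| Route | iCBT | Control |
|---|---|---|
| Weekly coaching calls (2.4, 2.6) | yes, over seven weekly themes | no (2.5) |
| Self-initiated contact with the study team (2.6) | yes | yes, not limited by arm |
| Telephone and email reminders (2.15) | yes, for retention | yes, for retention |
| Standard care (2.1, 2.5) | yes | yes, not described as a source of study adverse-event data |
| EPDS, BDI-II, GAD-7 at T2 (Table 3) | yes | yes |

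The contrast is therefore scheduled plus self-initiated contact against self-initiated contact alone. Symptom scores at T2 do not share this imbalance.

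**Illustration (assumed inputs)**

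From the article: n = 317 enrolled per arm (section 2.15). Assumed, not in the article: the same true event rate p in both arms (5%, 10% or 20%); capture of 90% with calls; capture of 60% or 30% without.

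- Expected recorded events = n × p × capture. At p = 10%: 317 × 0.10 × 0.90 = 28.5 under iCBT, against 317 × 0.10 × 0.60 = 19.0 or 317 × 0.10 × 0.30 = 9.5 under control.
- Observed risk ratio = ratio of capture rates, since p cancels: 0.90/0.60 = 1.5 or 0.90/0.30 = 3.0. The true ratio is 1.0.
- If the counts were tested, the chance of a significant excess under iCBT is Φ[(d − 1.96·SE0)/SE1]. Here d is the difference in observed rates, SE0 uses the pooled rate and SE1 the separate rates. For 9% against 6%: d = 0.03, SE0 = √(2 × 0.075 × 0.925/317) = 0.0209, SE1 = √((0.09 × 0.91 + 0.06 × 0.94)/317) = 0.0209, giving Φ(−0.53) = 30%. The nominal figure in that direction is 2.5%.

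| True rate, both arms | Capture without calls | Expected recorded events, iCBT v control | Risk ratio | Chance of a false significant excess |
|---|---|---|---|---|
| 5% | 60% | 14.3 v 9.5 | 1.5 | 17% |
| 5% | 30% | 14.3 v 4.8 | 3.0 | 60% |
| 10% | 60% | 28.5 v 19.0 | 1.5 | 30% |
| 10% | 30% | 28.5 v 9.5 | 3.0 | 89% |
| 20% | 60% | 57.1 v 38.0 | 1.5 | 56% |
| 20% | 30% | 57.1 v 19.0 | 3.0 | 99.7% |

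With equal capture the ratio is 1.0 and the chance is 2.5% at every rate. The normal approximation is rough where counts are small.

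**The case against.** The case on the other side is substantial.

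- **Harms are not ascertained in one arm only.** A reader who stops at the calls might infer that they are. The same sentence of section 2.6 also gives women open access to the study team, without limiting it to an arm. This stands: the imbalance is one of degree.
- **Deterioration among controls is not invisible.** A reader might infer that it is, or that every comparison of harms is biased. Table 3 schedules EPDS, BDI-II and GAD-7 at T2 for both arms, so worsening of depressive and anxiety symptoms can be compared on equal terms. This stands. What controls lack is a scheduled study contact for adverse effects between T0 and T2.
- **No biased comparison is planned.** Section 2.16 names no adverse-event analysis by arm, and no hypothesis concerns harms. This stands: the distortion appears only if the counts are set side by side.
- **Handling is not recording.** Section 2.6 says that adverse effects are handled in the calls, which may describe management and not data capture. Since it speaks of effects of the intervention, dealing with them in the intervention's own calls is coherent. So sections 2.5 and 2.6 are not in strict contradiction. This largely stands, but it leaves the section with no scheduled route common to both arms.
- **The article condenses a fuller protocol.** Definitions and recording forms may be set out there, so the lack of an adverse-event row in Table 3 is not in itself an error. This stands. The point rests on what section 2.6 does state: a scheduled route that one arm does not have.

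**Conclusion.** The point holds in a limited form. The one scheduled contact that the article ties to adverse effects is confined to the iCBT arm, and neither the retention reminders nor Table 3 supplies an equivalent for controls. Adverse-event counts collected on that basis should not be compared between arms. If they were, they would probably overstate harms under iCBT, on the assumption that weekly contact raises the share of events that come to light.

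The size cannot be derived from the article. The ratios of 1.5 and 3.0 are the assumed capture rates divided by each other: they show how the distortion would work and do not estimate it. It vanishes if capture is equal. The primary and secondary efficacy comparisons do not depend on this route. The issue is one of harms reporting, worth correcting because the correction is cheap.

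**What to change.** In section 2.6 and Table 3:

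1. Add the same short set of adverse-event items to the T2 questionnaire in both arms, and report the answers by randomized arm as the comparative harms data.
2. Report events raised in coaching calls separately, and state that they will not be compared between arms.
3. Tabulate by arm the share of women whose T2 EPDS exceeds their T0 EPDS. This uses data already collected.

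The cost is a few questionnaire items and a small amount of tabulation. Follow-up runs on both online and paper forms (section 2.14), so both must be revised while recruitment is ongoing (section 2.2). Women already past T2 will lack the new items, so the first table will cover only part of the sample and should say so; the EPDS tabulation is not affected by this. If the forms cannot be changed, items 2 and 3 can still be done. How events are handled clinically is left to the investigators.
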